#### Village doctors’ baseline questionnaire

The village doctors will complete a baseline questionnaire before the intervention to provide information on their personality and work, including the usual content of their work, years of work experience, salary and other incomes, revenue components, and additional relevant data.

#### Regional data

The research team will contact the local health committees to obtain relevant regional data, including HIV prevalence and all-cause mortality.

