### Study setting and recruitment

Members of the local Municipal Health Commission of Liangshan and the Liangshan village chiefs will help recruit participants through in-person outreach at the villagers’ residential locations. Two hundred villages in Liangshan are defined as clusters, with 20 families randomly selected from each village as the study’s target population. One adult from each family using a mobile phone with internet service will be randomly selected as the intervention participant. One village doctor from each village will be responsible for sending the HIV-related health education information to the participants living in that village. The participants can then share the information with other family members at their discretion. In this way, the research team can first examine the effects of the intervention on the participants, and then discuss the path of secondary information dissemination and the scope of the intervention.

At the beginning of the research, the researchers will confirm the eligibility of all the participants to ensure that they meet the recruitment criteria. The researchers will then introduce the research schedule and review the message delivery tools, WeChat and the Chinese Version of TikTok, with the village doctors and participants. Next, the village doctors and participants will fill out the informed consent form, on paper or electronically. Considering the villagers’ education level and illiteracy rate, the research team staff will thoroughly explain the form’s content and meaning to them before they sign it. If the villagers cannot print their Chinese names, their fingerprints will substitute as signatures.

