### Randomization and allocation

Randomization is done by the research team at the cluster level using a stratified randomization method, with each village defined as a cluster. First, each village will be assigned a number. Next, the cillage numbers will be extracted and randomized into three groups in a 1:1:1 ratio: (1) The “Control” group without any mobile-based message intervention; (2) “Intervention A” with village doctors delivering HIV-related intervention messages to the participants and receiving a standardized monetary compensation, and (3) “Intervention B” with village doctors delivering HIV-related intervention messages to the participants and receiving a monetary compensation, the amount of which will depends on how well the participants perform during the intervention.

In the entire process of data collection, management, and analysis, the staff members will not be informed of the randomization scheme. The data analyst will also not be informed until the results of the analysis obtained. Only the research team staff responsible for message delivery will be aware of which villages are assigned to each experimental group. The village doctors will not know the experimental group to which they belong or the differences between the three groups; this will prevent them from comparing their responsibilities, tasks, and monetary compensation with others in a different group, which could result in bias or a change in attitude toward their assignment. Furthermore, the village doctors will not be allowed to discuss with the participants of any group information about which the doctors have speculated.

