### Intervention modules

The experimental intervention method involves delivering mobile-based HIV-related messages in the form of texts, pictures, audio, and videos using WeChat and the Chinese Version of TikTok to improve the villagers’ HIV-related health literacy and protect them from AIDS infection.

The “Control” group participants will not receive the mobile-based intervention delivered by WeChat and the Chinese Version of TikTok. They will receive general disease-related information from the AIDS public health campaign and mass media such as TV, newspapers, and internet.

In addition to receiving general information from mass media and campaigns, the participants in the “Intervention A” and “Intervention B” groups will receive HIV/AIDS awareness-raising and behavior-related cyclical messages delivered by the village doctors on a biweekly basis for 18 months. Participants who are illiterate in Mandarin Chinese or have difficulty understanding the content of the messages can consult their village doctors on WeChat in the village group chat or in a private one-on-one conversation. They may request a translation of the message into the Yi ethnic group’s language or ask the doctor to clarify and explain its content.

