The content of the intervention is divided into eight modules, as shown in Fig. 2, along with the order of message delivery. Each module serves a unique purpose and function. (1) The basic HIV facts module mainly introduces basic information about HIV, such as its concept, origin, mechanism of action, survival rate, harmful damages to the human body, current global impact, and more. (2) The key populations module presents information on groups at higher risk of HIV/AIDS infection (e.g., MSM, IDUs, sex workers, and transgender people) and their associated characteristics to capture the participants’ attention and remind them to take protective measures if they are engaged in related work or have related behaviors. (3) The HIV transmission module provides information on the ways the virus can and cannot be transmitted and discusses the corresponding prevention methods. As one of the most critical parts of the intervention, this module includes three sub-modules with two topics each (Fig. 2). The transmission via sexual intercourse sub-module will highlight the knowledge, attitudes, skills, and values that lead to safer sex and introduce male and female condoms for defense against HIV and the correct ways to use them. The transmission via blood sub-module will introduce how contaminated blood transfusion, needle-sharing, needlestick injuries, open wound contamination, and other incidents lead to HIV infection. The sub-module will also provide an overview of the health complications and increased risk of HIV infection associated with drug use and emphasize China’s laws that regulate the manufacturing, trafficking, and usage of illicit substances. The mother-to-child transmission sub-module will share guidelines on the use of antiretroviral treatment during pregnancy, childbirth, and breastfeeding and present recommendations on breastfeeding for HIV-positive mothers to protect the infant’s health. (4) The HIV symptoms module introduces HIV-positive patients’ symptoms at different stages of the disease, the cirus's destruction of the body’s immunity, and the importance of seeking professional consultation when similar symptoms arise. (5) The HIV testing module includes reminders for the villagers to get tested regularly for HIV and direct them to available HIV self-tests, testing facilities and community centers, and testing procedures in Liangshan. (6) The HIV treatment module delivers messages on current HIV treatments and specific guidelines for various age groups. (7) The HIV laws module educates the participants on China’s HIV-related laws that protect the public and HIV/AIDS patients. (8) The harmful consequences module draws local villagers’ attention to the severe negative impacts of HIV/AIDS on public health, family, society, and the economy.

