#### Secondary outcomes

Effectiveness of secondary knowledge transmission from the participants to their family members will be determined. The research team will compare the path of knowledge dissemination directly to the participants and the path of secondary knowledge transmission to their family members; measure the attenuation, weakening, errors, and gaps in the retelling and sharing of knowledge; and assess the participants’ willingness to share the knowledge with their family members voluntarily. The research team will first compare the family members’ scores from the HIV-related knowledge follow-up questionnaires to that of their previous baseline questionnaire to identify any knowledge improvement, then compare the family members’ magnitude of improvement to that of the participants’ to identify weakening and gaps in knowledge sharing.

Behavioral changes (e.g., condom use and substance use), health outcomes (e.g., clinical characteristics, HIV prevalence, mental health, quality of life, and all-cause mortality), and social factors (e.g., stigma toward HIV and social support) will be measured by the instruments outlined in Table 1. The regional data on HIV prevalence and all-cause mortality will be obtained from the local health committee.

Feasibility of the intervention will be calculated by dividing the number of people who can use WeChat and the Chinese Version TikTok by the total number of people living in the area. These data will be collected during field studies before the experiment, where the research team will randomly distribute surveys in each village to inspect the local wireless network coverage and use of mobile phones.

Level of engagement will be measured by an original engagement and attendance scale. Participants will choose from a range of 1 to 6, with 1 representing non-engaging and 6 representing highly engaging.

Acceptability and satisfaction with the intervention will be assessed via an original questionnaire with rating scales. Participants will be asked to rate and provide feedback on the intervention’s content and method, including the effectiveness of the HIV-related knowledge modules, the time and method of information delivery, village doctors’ attitude and competence, the design of the entire experimental intervention process, and more.

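### HIV prevalence and all-cause mortality are named as secondary outcomes but measured only by regional records, which cannot give a sound comparison between arms

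*Protocol article*

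**What the plan says.** The Secondary outcomes section names "health outcomes (e.g., clinical characteristics, HIV prevalence, mental health, quality of life, and all-cause mortality" among what the trial will measure. It gives the source of two of these: "The regional data on HIV prevalence and all-cause mortality will be obtained from the local health committee". The Regional data section agrees, having the team "obtain relevant regional data, including HIV prevalence and all-cause mortality" from the health committees, and Table 1 enters regional data as the measure for both, at baseline and at follow-up. No other source is described for either.

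The Randomization and allocation section makes the village the unit, with villages "randomized into three groups in a 1:1:1 ratio". The Study setting and recruitment section has "20 families randomly selected from each village" and one adult per family as the message recipient, who may share the content at home. The Data analysis section plans tests of differences between groups at 6, 12 and 18 months.

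The Intervention modules section states that "The HIV testing module includes reminders for the villagers to get tested regularly for HIV", and that it points them to self-tests and testing sites. It also states that Control "participants will not receive the mobile-based intervention delivered by WeChat and the Chinese Version of TikTok".

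**The concern.** An outcome can show an intervention effect only if it is observed on units that can be assigned to an arm, and if enough of what it counts was exposed. The documents secure neither for these two measures.

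There is a further problem for HIV prevalence. If the committees' figure counts diagnosed infections, it rises when more people test. The testing module seeks that behaviour in A and B and does not reach Control by the same route. Ascertainment could then differ by arm in the direction opposite to prevention.

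At stake is how the health results are read. A null result could be taken as no health effect when the measure could hardly move. A rise in recorded prevalence in A or B could be taken as failure when it reflects the testing that the module asks for.

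**Working it through.** The article gives no expected value, effect size or power for these two outcomes, so there is no figure of that kind to reproduce. Its enrolment figures do reproduce: 66 × 20 × 0.80 = 1,056 per arm after attrition, and 66 × 3 × 20 = 3,960 in all. Enrolled per arm: 66 × 20 = 1,320.

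**Inputs from the article:** 66 villages per arm, 20 recipients per village, 18 months, background prevalence of 2.88% to 9.46% in the Yi population (Background).

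**Assumptions, not in the article:** village size 500 to 1,500; incidence 0.1% to 0.5% a year; 4 persons per household; 10% to 30% of infections undiagnosed. Step 4 uses its own stated values.

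**1. Records above village level.** All villages lie in one prefecture and arms are allocated by village. A county or prefecture figure can therefore pool villages of all three arms, and no arm contrast can be formed.

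**2. Records at village level: dilution.**
- Share reached, recipients only: 20/500 = 4% to 20/1,500 = 1.3%.
- Share reached with family sharing (80 persons): 80/500 = 16% to 80/1,500 = 5.3%.
- Infections averted per arm if every recipient infection is prevented: 1,320 × 1.5 × 0.001 = 2.0 to 1,320 × 1.5 × 0.005 = 9.9.
- Per village: 20 × 1.5 × 0.001 = 0.03 to 20 × 1.5 × 0.005 = 0.15.
- Change in village prevalence: 0.03/1,500 = 0.002 to 0.15/500 = 0.03 percentage points.
- With all 80 persons reached, four times as much: 0.008 to 0.12 points for complete prevention, or 0.0024 to 0.036 points for a 30% reduction.

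The same shares apply to mortality: a village-wide death rate shows about 1.3% to 4% of any effect in recipients, or 5.3% to 16% if whole households are counted.

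**3. Detection on the same scale (prevalence only, if records count diagnosed cases).** Suppose all 1,320 participants test and all of that testing is in excess of Control:
- Added diagnoses per arm: 1,320 × 0.0288 × 0.10 = 3.8 to 1,320 × 0.0946 × 0.30 = 37.5.
- Change in village prevalence: 3.8/66/1,500 = 0.004 to 37.5/66/500 = 0.11 percentage points.

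These ranges overlap those for prevention. At incidence 0.5%, prevalence 2.88% and 10% undiagnosed, 9.9 averted infections exceed 3.8 added diagnoses. Elsewhere in the ranges the order is reversed.

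**4. Can the sign reverse with partial effects?** Take 80 of 1,000 residents reached (f = 0.08), 18-month incidence i = 0.75% cut by 30% among those reached, and diagnosed share rising from 60% to 80% among those reached.
- Control recorded prevalence = (p + i) × 0.60.
- Intervention recorded prevalence = (1 − f)(p + i) × 0.60 + f(p + 0.7i) × 0.80.
- p = 2.88%: 2.178% against 2.222%.
- p = 9.46%: 6.126% against 6.275%.
- True prevalence meanwhile falls by 0.08 × 0.75% × 0.30 = 0.018 points.

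The break-even diagnosed share is 0.60(p + i)/(p + 0.7i), which is about 64% at p = 2.88% and 61% at p = 9.46%. Over 18-month incidence of 0.25% to 1.5% and reductions of 30% to 50%, it runs from 60.5% to 72.4%. A reversal is possible with a modest rise in diagnosis, but the recorded differences in this example are only 0.04 and 0.15 points.

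**The case against.** Several objections have force.

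- **The nature of the records is not stated.** They could be case reports, sentinel surveillance or a serosurvey. That they count diagnosed cases is an inference, and so is any rise in diagnoses from the module. This stands, so the detection argument is conditional.
- **A reader might infer that detection will outweigh prevention, so that an effective arm will look worse.** The documents do not support this. The ranges overlap, one corner goes the other way, and the detection figures assume complete uptake. Detection is also diluted in village-wide data, as prevention is.
- **A reader might extend the detection argument to mortality.** It does not apply there; only the attribution and dilution points do.
- **Reach is wider than 20 people, and Control is not without information.** Recipients may share with family, and Control has the public campaign and mass media. Both points are fair. Family sharing is included above and still leaves most residents unreached at the assumed village sizes. The mobile testing reminders remain confined to A and B.
- **The geographic level may be given in a fuller protocol.** It may, and its absence from an article is not the fault raised here. Knowing it would only choose between no arm contrast and a heavily diluted one.
- **No decision rule, power claim or primary outcome rests on these measures.** This is true, and it limits the seriousness. They are still listed as outcomes of an intervention that aims to improve health outcomes.

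**Conclusion.** The point holds in a limited form. As sourced, neither HIV prevalence nor all-cause mortality can serve as a sound between-arm outcome. Above village level there may be no contrast at all. At village level, complete prevention among recipients would move prevalence by 0.002 to 0.03 percentage points, under assumed village sizes of 500 to 1,500 and incidence of 0.1% to 0.5% a year. Full household sharing raises this to at most 0.12 points, and to at most 0.036 points for a 30% reduction.

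For prevalence only, and only if the records reflect diagnosed cases, differential testing could partly or wholly mask a preventive effect, or reverse it. The size and net sign depend on incidence, undiagnosed share and test uptake, none of which the article gives. These are secondary outcomes, and the knowledge comparison is not affected.

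**What to change.** In the Secondary outcomes section and Table 1, relabel HIV prevalence and all-cause mortality as descriptive regional context and not as between-arm effectiveness outcomes.

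If the health committees can supply village-level counts, report HIV tests done and new diagnoses by arm beside prevalence. State in advance that more testing and more diagnoses in A and B are an expected effect of the testing module and not evidence of harm.

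The cost is a change of wording and the loss of two nominal secondary outcomes to descriptive status. The regional data can still be collected as planned.

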### Follow-up surveys

Follow-up assessments, identical to the baseline questionnaires, will be scheduled at 6, 12, and 18-month periods. The participants and their family members will be offered financial compensation of 20 CNY for their completion of the questionnaires at the designated times.

### Randomization and allocation

Randomization is done by the research team at the cluster level using a stratified randomization method, with each village defined as a cluster. First, each village will be assigned a number. Next, the cillage numbers will be extracted and randomized into three groups in a 1:1:1 ratio: (1) The “Control” group without any mobile-based message intervention; (2) “Intervention A” with village doctors delivering HIV-related intervention messages to the participants and receiving a standardized monetary compensation, and (3) “Intervention B” with village doctors delivering HIV-related intervention messages to the participants and receiving a monetary compensation, the amount of which will depends on how well the participants perform during the intervention.

In the entire process of data collection, management, and analysis, the staff members will not be informed of the randomization scheme. The data analyst will also not be informed until the results of the analysis obtained. Only the research team staff responsible for message delivery will be aware of which villages are assigned to each experimental group. The village doctors will not know the experimental group to which they belong or the differences between the three groups; this will prevent them from comparing their responsibilities, tasks, and monetary compensation with others in a different group, which could result in bias or a change in attitude toward their assignment. Furthermore, the village doctors will not be allowed to discuss with the participants of any group information about which the doctors have speculated.

### Preparation for the intervention

The tools that will be used for the intervention are WeChat and the Chinese Version of TikTok (Douyin in Chinese). WeChat is an instant messaging application that is widely used in China for communication. The number of active Wechat users reached 1.27 billion in 2021 Q4 (with a total population of 1.41 billion), making it convenient for distributing HIV-related information via text, voice, graphics, and video messages. The Chinese Version of TikTok is the most popular short video-sharing platform in China, and it can be used to share HIV-related educational videos with the study participants. A data collecting application alled Interviewer will be used to collect demographic and economic information from the participants. The use of these applications facilitates the management of stakeholders and ensures effective dissemination of information.

The research team will create a WeChat account with three group chats: “Control,” “Intervention A,” and “Intervention B.” Doctors in the control and intervention groups are required to add the research team’s WeChat account as a contact, enter the specified intervention group chat, and create a new group chat to connect with participants in their village. HIV-related intervention content will be delivered from the research team to the village doctors through their assigned intervention group chat and then forwarded to the participants by the village doctors in the group chat they previously created. The research team will also create two accounts for the Chinese Version TikTok, representing “Intervention A” and “Intervention B.” Village doctors and participants in the intervention groups are required to follow their corresponding accounts for the Chinese Version TikTok. The research team will post identical HIV-related short educational videos on both accounts, and the village doctors will share the videos with the participants in the WeChat group. The research team will monitor and compare the numbers of views and likes each account receives as an indicator of the effectiveness of the village doctors in promoting the videos to the participants in the two intervention groups.

Before implementing the study, all the village doctors will receive 10 four-hour training sessions on the participant recruitment process, data collection procedures, intervention modules, answers to frequently asked questions, use of intervention tools, and work quality expectations. To protect the participants’ privacy and confidentiality, the research team staff will compile a unique ID for each participant to hide their personal information, including name, national identification number, and phone number during the data processing stage.

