The study has several objectives. First, to improve Liangshan residents' knowledge, attitudes, and practices regarding HIV/AIDS. Second, to determine the effect of monetary compensation on incentivizing village doctors’ dissemination of information. Third, to evaluate the path of secondary knowledge transmission from direct participants to their family members. Fourth, to test the efficacy, accessibility, convenience, and participants’ satisfaction towards the mobile-delivered intervention. Lastly, to evaluate how social, economic, cultural, cognitive, and behavioral factors influence information dissemination and comprehension, resulting in various effects of the intervention.

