### Village doctor incentives and performance monitoring

For both the control and intervention (A and B) groups, the village doctors will receive a monetary reward for every questionnaire the participants fill out. In the “Control” group in which village doctors do not deliver any mobile-based HIV-related intervention messages, the monetary reward for participants’ completion of questionnaires is the village doctors' only financial incentive.

For the “Intervention A” group, in addition to the reward from participants completing the questionnaires, the village doctors will also receive a standardized monetary compensation of 200 CNY per month for sending the mobile-based HIV-related intervention messages to the participants. The research team will randomly select, contact, and conduct phone interviews with participants every month to assess the village doctors’ work performance. During the phone interviews, participants will be questioned on the following: (1) the village doctors’ completion of the assigned tasks, determined by whether the participants received effective HIV-related information transmission on a biweekly basis; (2) their understanding of key knowledge points; and (3) their satisfaction with the doctors’ attitude, competence, and willingness to explan and clarify the messages. The phone interviews will be recorded for subsequent analysis.

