For the “Intervention B” group, in addition to the reward for participants completing the questionnaires, the village doctors will also receive a varying amount of monetary compensation, ranging from 0 to 400 CNY, for sending the mobile-based HIV-related intervention messages to the participants. Intervention B’s financial incentive is designed to encourage and empower village doctors to perform their duties more efficiently and enthusiastically to obtain the highest reward. Similar to Intervention A, the research team will randomly select participants for monthly phone interviews. During the phone interviews, participants’ answers to the questions in each of the three portions of the interview assessment will be scored: (1) the village doctors’ completion of the assigned tasks accounts for 30 points, (2) the villagers’ understanding of key knowledge points accounts for 50 points, and (3) participants’ satisfaction with the doctors’ attitude, competence, and willingness to explain and clarify the messages accounts for 20 points. A participant may score anywhere from 0 to 100 points. If the average score of all the selected participants from one village is 100 points, their assigned village doctor will receive 400 CNY per month. Scores lower than 100 will correspond to a lesser amount of money (e.g., a score of 50 points corresponds to 200 CNY per month).

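### TikTok account totals give one value per arm, so they cannot show whether pay type changes doctors' dissemination; the interviews held in both arms could, but are described as scored only in B

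*Protocol article*

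**What the plan says.** The objectives at the end of Background include "to determine the effect of monetary compensation on incentivizing village doctors’ dissemination of information".

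Under Preparation for the intervention, the article says: "The research team will also create two accounts for the Chinese Version TikTok, representing “Intervention A” and “Intervention B". It adds that "The research team will post identical HIV-related short educational videos on both accounts", and that "Village doctors and participants in the intervention groups are required to follow their corresponding accounts for the Chinese Version TikTok". The team will then "monitor and compare the numbers of views and likes each account receives as an indicator of the effectiveness of the village doctors", meaning their promotion of the videos. Nothing there describes attributing counts to a village or participant, or restricting who can view the accounts.

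Under Village doctor incentives and performance monitoring, randomly selected participants in arm A are interviewed by phone every month to assess the doctors' work. The interview covers task completion, understanding of key points and satisfaction. For A the article says: "The phone interviews will be recorded for subsequent analysis". For B it describes similar monthly interviews, in which answers to "each of the three portions of the interview assessment will be scored", with 30, 50 and 20 points. The mean over a village's selected participants sets that doctor's pay, from 0 to 400 CNY per month. No comparison of interview scores between A and B is stated.

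Under Primary outcomes, A versus B is judged by participants' knowledge improvement and by cost-effectiveness. TikTok counts do not appear there, in Table 1 or under Data analysis.

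**The concern.** The article presents views and likes as a sign of how effective the doctors are, and compares them between two arms that differ in how doctors are paid. A reader of the results would take a higher total in B as evidence that performance pay worked. The total cannot bear that reading: villages are randomised, but the figure exists only for the whole arm. It also mixes what doctors do with what happens without them. Participants must follow the account, so they can watch a video that no doctor shared, and doctors' own views can count too.

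At stake is the dissemination objective. Knowledge scores lie downstream of delivery. If knowledge does not differ between A and B, they cannot tell whether pay failed to change delivery or whether better delivery failed to raise knowledge. A direct measure of delivery is needed for that, and the one compared between arms is not usable.

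**Working it through.** **Inputs from the article**
- Clusters per arm: 66; analysed per arm: 1,056; retention 80%; 20 per cluster; 3,960 in total (Sample size calculation).
- Unit of randomisation: the village (Randomization and allocation), with one doctor per village (Village doctors).
- TikTok accounts: two, one each for A and B (Preparation for the intervention).
- Interviews: monthly, over an 18-month intervention (Village doctor incentives and performance monitoring; Study design overview).

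**The plan's own figures**
- 1,056 / 66 = 16 analysed per cluster; 16 / 0.80 = 20 enrolled per cluster; 66 × 20 = 1,320 enrolled per arm; 1,320 × 3 = 3,960. These reproduce and are not in dispute. They fix the number of villages available for an A-versus-B comparison.

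**Units behind each measure**
- Account totals: 1 value in A and 1 in B. Residual degrees of freedom = 2 − 2 = 0, so no village-level standard error can be formed.
- Village means from the interviews: up to 66 + 66 villages. Residual degrees of freedom = 132 − 2 = 130.
- Scores per village: at most 18, hence at most 66 × 18 = 1,188 village-months per arm. This is an upper bound, because the article does not say that every village is sampled every month. Repeated scores sharpen a village's mean, but the sample size for the comparison remains the number of villages.

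**What village means could detect**

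Two-sided α = 0.05, normal approximation, all 66 villages per arm contributing. Detectable difference = (z for α/2 + z for power) × √(2/66), in units of the between-village SD of the village mean. √(2/66) = 0.174.
- 80% power: (1.960 + 0.842) × 0.174 = 0.49 SD.
- 90% power: (1.960 + 1.282) × 0.174 = 0.56 SD.
- Power for a true difference of 0.3, 0.4, 0.5 and 0.6 SD: 41%, 63%, 82% and 93%.

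The article gives no SD for the interview score, so these cannot be turned into points.

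**Illustration of fragility (assumed figures)**

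Suppose 50% of the 1,320 enrolled in A and 60% of those in B view a video once: 660 and 792 views, ratio 792 / 660 = 1.20. Now add views that come from no enrolled participant.
- 132 (10% of enrolment) on A only: 792 / (660 + 132) = 1.00.
- 132 on B only: (792 + 132) / 660 = 1.40.
- 1,320 on each account: (792 + 1,320) / (660 + 1,320) = 1.07.

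This shows sensitivity only. The article gives no basis for any particular number of outside views.

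**The case against.** The strongest reply is that the counts are a side indicator. They appear once, in a section on set-up, as one indicator of video promotion. No test on them is proposed, and the A-versus-B primary question is answered by other means. This stands as to the primary outcome: a reader might infer that TikTok totals are how the incentive question is decided, and Primary outcomes says otherwise. It does not rescue the indicator. Comparing the totals as a sign of doctors' effectiveness invites a conclusion about pay type whether or not a p-value is attached.

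The article also has another measure of doctors' work, since the A interviews are held for that purpose. That stands too, so it would be wrong to say that nothing else bears on delivery. What is absent is a stated comparison of that measure between arms.

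A reader might infer that the A interviews will go unscored. The documents do not support this: scoring in A is not described, but the recordings are kept for analysis, and B's points are spelled out because they set pay. Coding details may sit in a fuller document that is not shown. The point therefore rests on the comparison that the article does state.

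A reader might likewise infer that outsiders will inflate the counts. The article does not say whether the accounts are open or closed, so this is only a possibility. The lack of village-level information, and the views that arise without any doctor's effort, remain even with closed accounts.

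Finally, the interview score is not neutral: it sets pay in B and not in A, so B doctors alone gain from favourable reports. This is a real limitation of the remedy.

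**Conclusion.** The point holds within limits. Comparing account totals supplies one value per arm, with 0 residual degrees of freedom, and cannot be attributed to any of the 66 planned villages or their doctors. It should not be offered as evidence of doctors' effectiveness. The stated evaluation of the second primary outcome is untouched. The loss is confined to the dissemination objective, which has no usable direct A-versus-B comparison as written.

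The interviews could supply one with up to 66 villages per arm, enough to detect about 0.49 between-village SD at 80% power or 0.56 SD at 90%. This assumes that every village contributes at least one interview and that the interviews are conducted and scored alike in both arms. If fewer villages are sampled, the detectable difference grows. The change is worth making, because it uses data the trial already plans to collect.

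**What to change.** 1. Score the arm A interviews on the same 30/50/20 scale as B, with no effect on A doctors' pay. Use existing staff who do not know the arm. For that to work, the same people should score interviews from both arms, mixed and identified only by code.
2. Compare the village-mean task-completion component (the 30-point part) between A and B, with the village as the unit, as the supporting measure of dissemination. Report how many villages and how many interviews per village contribute.
3. Report TikTok views and likes descriptively, and remove the wording that treats them as an indicator of doctors' effectiveness.
4. State that the score determines pay only in B and may therefore favour B, and read it alongside the knowledge results from the separate follow-up surveys.

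The cost is scoring time for interviews already planned in A, plus a change of wording. Randomisation, the intervention, doctors' pay and the interview schedule stay as they are. The possible bias towards B is not removed by blinded scoring, because it can enter through what participants report.
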